### Sampling Method

To recruit participants, we will post a targeted (based on our inclusion criteria), clickable banner advertisement on Facebook. After clicking on the advertisement, potential participants will be redirected to our website. Those who meet our eligibility criteria and have granted informed consent will be sent a unique trial verification code via text message and email. This unique trial verification code will be used to take our survey. Moreover, participants eligible for this trial will be entered into a lottery draw with a 1:100 chance of receiving US $20.

### Study Setting

The Kingdom of Swaziland, situated in Southern Africa, is a small land-locked country, the area of Swaziland is estimated to be 17,364 km^2^ with an estimated population of 1,146,050 (2006) [19]. According to Facebook there are currently approximately 160,000 people on Facebook, of those, 97,000 of them are man and women between the ages of 18- and 29-years old. Our primary recruitment site will be Facebook. Facebook is one of the most widely used social networking platforms in Swaziland and allows for targeted advertisements specifically to send people to our website. These two factors make Facebook an ideal platform to reach the Internet population in Swaziland. Participants do not need to be Facebook users to participate in the trial because our website can be assessed directly from the Internet. Participants will not be discouraged to share the study website link on other platforms, such as WhatsApp, Instagram, Email, and others.

### Description of the Intervention

SwaziYolo (a smartphone game) is an interactive, educational story game that puts the player in the role of a young adult looking for love in Mbabane (the capital city of Swaziland), making important choices about relationships and sexual health (see Multimedia Appendix 1 for an overview of the steps taken in developing the intervention). The intervention is guided by cognitive-based approaches such as the Theory of Planned Behavior to target intentions to engage in HIV protective behavior [20-22] and the Health Belief Model to target perceived susceptibility of acquiring HIV infection [20]. While capitalizing on elements of serious games such as immersion, role-playing, and a dynamic storyline, the game exists in two major parts: the first is set in an imaginary social network called SwaziYolo, which is meant to resemble a combination of existing tools like Facebook, OKCupid, and Whatsapp. Here, players register (registration and login screen), view pictures (potential love interests “Connections” screen) and profiles of potential love interests (profile mode screen), and have Web-based chats (chat mode screen) with various characters. The other half of the game takes place in various made-up locations around Mbabane, such as nightclubs and cafes (meet up at a club screen) where players regularly go on dates referred to in the game as “meet-ups.” In both parts of the game, players are regularly required to choose between several courses of action to progress a conversation or storyline with a friend or love interest (chat mode screen). The decisions they make will influence the opinions and behavior of other characters, as well as the player’s own health and safety. Eventually, feedback is given based on choices made (feedback from a medical doctor at a clinic screen). In the game, the various character dialogues and scenes, will address the issues identified in our formative research such as HIV risk perception, raising knowledge of their own HIV status as well as a sexual partner’s HIV status, reducing multiple concurrent sexual partnerships, and consistent condom use.

The goal of the game is to maintain relationships with the characters, while staying healthy and happy. Once all the interactions with the characters have been completed, the game will give feedback on choices made and the risks those choices might carry. The game is expected to have an immense appeal to the youth, as an exciting new way to use their smartphones (see Figure 2 for the actual SwaziYolo screenshots). Participants in the wait-list control condition will complete the baseline and the immediate posttest measures as those in the SwaziYolo intervention condition, but will not play the game until the post-intervention assessment.

### Game Play

Player’s curiosity to “know what happens when they make a choice” is key to user engagement. The game’s narrative is primarily concerned with matters of sexual health, especially as it relates to HIV. Players will usually find themselves in situations where they have to make important decisions about their health, for example, resisting the pressure to have unprotected sex. The game keeps track of how well a player’s relationship is going with other characters using “TRUST” ratings (intimacy ratings), and a “YOLO” rating: how safe (safe relates to making choices that do not expose player to HIV risk) they have been during the course of the game. While players enjoy game play, they are exposed to valuable learning situations and are encouraged to care more about the various characters. Some will give good advice, while others will find themselves in difficult situations where they ask other players for help and guidance.

**Figure 2 figure2:**
[figure not shown]
SwaziYolo screenshots.

### Sample Size Calculation

The trial will be powered on the primary outcome measure and based on comparison of the change in HIV risk perception score from pre- to post-intervention assessment in the intervention group at 4 weeks. A study conducted in Uganda estimated mean HIV risk perception of M=3.27, SD *=* 1.03, therefore, we used this estimation as our baseline mean and SD to calculate our effect size [21]. Assuming a moderate effect size of 0.477 (identified by Chu et al [22]), alpha (two-tailed)=0.05, beta=0.20, with 1:1 allocation ratio between both groups, and a SD of the outcome in the population of 1.03, the total sample required to sufficiently power the study would be 146 (73 for each group). Moreover, assuming a 30% loss to follow-up rate [15], we then inflated the sample by 30% to yield a sample of 190. After that, we considered gender differences and once more inflated the sample by a factor of 2 to give a final sample size of 380. Finally, to ensure a balance between males and females in both groups we will recruit 190 females and 190 males. The sample size was calculated using Web-based sample size calculation software [23,24].

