### Randomization

Upon confirmation of participants’ trial registration, participants will be assigned another unique code called “game unlock code,” which will be used for randomization using secure, remote, Web-based computer software within 24 hours of recruitment. As stated in the research design, participants will be randomized into 2 groups; the intervention group and the wait-list control group in a 1:1 ratio. The data analysis team will be blinded in this study, however, participants will not be blinded.

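### Adding 30% to 146 does not cover 30% loss (190 leaves 133 completers; 209 are needed), the doubling for gender matches no stated analysis, and a 190/190 quota does not balance the arms

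*Protocol article*

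**What the plan says.** The Sample Size Calculation section of the Protocol article builds the target in three steps.

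- **Base size.** The inputs are "alpha (two-tailed)=0.05, beta=0.20, with 1:1 allocation ratio between both groups", with "Assuming a moderate effect size of 0.477" and "a SD of the outcome in the population of 1.03". They lead to 146 in total, 73 per arm.
- **Loss to follow-up.** "assuming a 30% loss to follow-up rate [15], we then inflated the sample by 30% to yield a sample of 190".
- **Gender.** "we considered gender differences and once more inflated the sample by a factor of 2 to give a final sample size of 380". The section then adds: "to ensure a balance between males and females in both groups we will recruit 190 females and 190 males".

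The Randomization section describes web-based software and says that "participants will be randomized into 2 groups; the intervention group and the wait-list control group in a 1:1 ratio". It mentions no stratification or minimisation. None of the five hypotheses under Study Design and Hypotheses concerns gender. In the analysis of the primary outcome, gender is one covariate in a linear regression that is run if baseline differences are seen. The one named subgroup, under the secondary outcomes, is defined by low risk perception and no condom use.

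**The concern.** Three things in one short section do not follow.

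1. The allowance for loss uses n × (1 + d) where it needs n / (1 − d), so the number left after the assumed loss falls below the number the calculation says is required.
2. Half of the recruitment target rests on gender, yet no stated hypothesis or analysis uses that half. A covariate in a conditional regression does not call for twice the sample.
3. A recruitment quota fixes how many women and men enter the trial. It does not fix how they divide between the arms, which is what the article says it will ensure.

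At stake is whether 380 is correctly justified, how a by-sex result could be read if one were reported, and whether the promised balance is delivered. The balance point is time-sensitive, because the randomisation scheme cannot be changed retrospectively and the article says the study has not yet started.

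**Working it through.** **Inputs** (Sample Size Calculation): two-sided alpha 0.05, power 0.80, difference 0.477, SD 1.03, 1:1 allocation, loss 30%, gender multiplier 2.

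**1. Reproduce the base size.** n per arm = 2 × [SD × (z₀.₉₇₅ + z₀.₈₀) / difference]² = 2 × [1.03 × (1.960 + 0.842) / 0.477]² = 73.2. The article's 73 per arm (146) is this figure rounded down; rounding up gives 74 (148). Reading 0.477 as a standardised effect gives 69 per arm (70 by t test), which does not reproduce 146. So 0.477 is treated here as a raw difference with SD 1.03.

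**2. Reproduce the inflation and compare.**

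| Step | Article | Needed for 30% loss |
|---|---|---|
| Inflate 146 | 146 × 1.30 = 189.8 → 190 | 146 / 0.70 = 208.6 → 209 |
| Completers after 30% loss | 190 × 0.70 = 133 | 209 × 0.70 = 146.3 |
| Double for gender | 380 | 418 |
| Completers after 30% loss | 380 × 0.70 = 266 | 418 × 0.70 = 292.6 |

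The loss that 190 can absorb is 1 − 146/190 = 23.2%. After doubling, the shortfall against 2 × 146 = 292 is 26 completers. (Equal arms would make the corrected figures 210 and 420.)

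**3. Power that 380 gives with 30% loss.** SE = 1.03 × √(2/n per arm); power = Φ(0.477/SE − 1.96).

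- All participants, 133 per arm: SE = 0.126, power 96.5% (96.4% by t test).
- One sex, 133 completers or 66.5 per arm: SE = 0.179, power 76.1% (75.5% by t test).
- The pooled comparison falls below 146 completers only if loss exceeds 1 − 146/380 = 61.6%.

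With 0.477 taken as standardised, the pooled and one-sex figures by t test are 97.2% and 77.9%, so the picture does not depend on that reading.

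**4. Balance from a 190/190 quota.** Under simple 1:1 randomisation, the number of the 190 women in one arm is binomial(190, 0.5), with a 95% range of 82 to 108. The chance of being more than 10 away from 95 is 12.7%. If the arm totals are fixed at 190 each but sex is not controlled, the hypergeometric 95% range is 85 to 105, or 45% to 55% women in the arm (85/190 to 105/190).

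**The case against.** The strongest reply is that the slip does no harm to the comparison the trial is powered on. The primary hypothesis concerns all participants, and 266 expected completers is far above 146. That stands in full, and it sets the severity.

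Second, the article is a condensed account. Stratification settings or a by-sex analysis could be in a full protocol or analysis plan that is not shown. This stands in part: silence about stratification is not itself an error, and the Randomization section does not say that allocation is simple. But the article names the recruitment quota as the means of ensuring balance in both groups, and a quota cannot do that. The imbalance to be expected is also modest, and the regression can adjust for gender.

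Third, a reader might infer from the doubling that the article promises 146 completers, or 80% power, within each sex, and then fault 380 for missing that promise. The document does not support this. It says only that gender differences were considered, and states no completer target or power by sex. The same goes for a sex-by-arm interaction. Power for a difference of 0.477 between the sexes would be about 47% (SE = 1.03 × √(4/66.5) = 0.253), but no such test is planned, so low power for it is not a failure of a stated aim.

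None of this rescues the inflation step, which is wrong from the article's own figures.

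**Conclusion.** The point holds in three limited parts.

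- **Inflation.** 190 is the wrong result for 30% loss. It should be 209, and 418 after the doubling. This is certain, since it uses only figures in the article.
- **Doubling.** It corresponds to no stated hypothesis or by-gender analysis, so the stated reason does not justify the factor of 2.
- **Balance.** Recruiting equal numbers of each sex does not ensure balance within arms. The 82–108 and 85–105 ranges assume that allocation takes no account of sex, which the article neither states nor rules out.

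It would be wrong to conclude that the trial is underpowered. The pooled primary comparison has about 96% power with 30% loss. That figure rests on the plan's inputs: a difference of 0.477, and an SD of 1.03 taken from a baseline risk-perception score in another study and applied to a change score here. Severity is minor to moderate: the written justification and the balance claim need correcting, but the primary comparison is not at risk from this error.

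**What to change.** Keep 380 and replace its derivation, rather than carrying the corrected chain through to 418.

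1. State: 380 randomised; 30% loss; 266 expected completers (133 per arm); about 96% power for the pooled comparison at a difference of 0.477 and SD 1.03. Where an allowance for loss is shown, use n/(1 − 0.30).
2. Say what the doubling was for. If it was to power each sex separately, state that 380 gives about 75–76% power within a sex rather than 80%. Label any by-sex or interaction result exploratory. If it was not, drop the gender rationale.
3. Stratify the web randomisation by sex, or minimise on sex, so that the stated balance is delivered. Describe the 190/190 quota as fixing the overall mix only.
4. Retain sex in the adjusted regression, which already lists it.

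The cost is a few reworded sentences and one setting in the randomisation software, made before enrolment begins. No extra participants are needed.

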### Randomization

Upon confirmation of participants’ trial registration, participants will be assigned another unique code called “game unlock code,” which will be used for randomization using secure, remote, Web-based computer software within 24 hours of recruitment. As stated in the research design, participants will be randomized into 2 groups; the intervention group and the wait-list control group in a 1:1 ratio. The data analysis team will be blinded in this study, however, participants will not be blinded.

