**User experience**			
	Would you recommend the game to your friends?		X
	How did you hear about this game?		X
	Number of times player reached the end of the game		X
	Level of satisfaction about the game		X

^a^Timing of assessment.

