#### Four-Weeks Follow-Up Data Collection

Trial participants will be followed-up for 4 weeks, the game will collect log data and send this data to our servers when the participant goes on the Internet, this will allow us to assess the exposure to the intervention without over burdening our participants to manually send us their usage data. Data captured will be limited to login data. In addition to this, a Web-based questionnaire will be sent to participants at the end of the follow-up period. Participants who will miss their 4-week follow-up assessment will be actively traced though phone calls and text messages.

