### Data Management and Statistical Analysis

#### Data Quality Assurance

First, Web-based questionnaires must be usable even for less experienced and knowledgeable Internet users [31], therefore we will exploit specific technical possibilities offered by open source Web-based questionnaires, such as visually highlighting buttons and predefined input fields. Additionally, we will use help features and input checks to assist participants when filling out the Web-based questionnaire. Beyond this, we will pilot test all filters and instructions given in the questionnaire. Second, to limit undesired multiple participation [32], either at baseline assessment or follow-up assessment, “sessions” will be used together with a verification code that participants will receive upon giving informed consent. Third, a specific problem that is faced by Web-based surveys is that respondents may “click through” the questionnaire, a phenomenon that becomes apparent when the interview is completed in less than the theoretical minimum time [31], therefore, the responses will be checked for plausibility and consistency and inconsistent records will be documented and censored from the final analysis.

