#### Primary Outcome Measure: HIV Risk Perception Score

First, we will use bivariate analysis to calculate the mean between baselines and follow-up. Next, to estimate the difference between the 2 groups, we will calculate the difference between the mean change of the intervention group and the mean change of the wait-list control group using two-sample paired *t* test. We will not perform interim analysis.

Secondly, in the case that, even after randomization, we observe some baseline differences, we will use multiple linear regression to adjust for those differences; where the outcome will be the follow-up score and the independent variables will be the intervention group, baseline scores, age, gender, marital status, level of education employment status, current monthly income, and number of times players played SwaziYolo. We will present our results in standardized regression coefficients for the intervention effect on the outcome variable as previously done for this type of hypothesis [25].

Although great effort will be put to minimize attrition, it is common for eHealth trials to typically have substantial attrition [26]. For this reason, our primary outcome analysis will prioritize analysis of the subjects who adhered to their group assignment and were sufficiently exposed to the intervention. Therefore, both pre-protocol analysis (as treated analysis) as well as intention to treat analysis will be done and both results will be reported. The approach of conducting both “intention to treat analysis” together with “as treated analysis” has been observed in literature for example, Weinstein and colleagues [33] followed this approach in their randomized trial comparing surgical versus nonoperative treatment for lumbar disk herniation.

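### The claim that the data analysis team is blinded cannot hold for the exposure-based analysis or the play-count regression, and should be limited to the intention-to-treat analyses

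*Protocol article*

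**What the plan says.** Blinding is stated once, in the Randomization section of the protocol article: "The data analysis team will be blinded in this study, however, participants will not be blinded". No part of the analysis is excepted.

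Description of the Intervention says that wait-list controls complete the same assessments "but will not play the game until the post-intervention assessment".

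Three other sections bring game-use data into the data set or the analysis:

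- **Primary Outcome Measure: HIV Risk Perception Score.** The primary outcome analysis "will prioritize analysis of the subjects who adhered to their group assignment and were sufficiently exposed to the intervention". If baseline differences are seen, a multiple linear regression is fitted. Its independent variables include the intervention group and, at the end of the list, "current monthly income, and number of times players played SwaziYolo".
- **Four-Weeks Follow-Up Data Collection.** During follow-up "the game will collect log data and send this data to our servers when the participant goes on the Internet", so that exposure can be assessed.
- **Table 1, User experience.** The 4-week questionnaire includes "Number of times player reached the end of the game" and "Level of satisfaction about the game".

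Data Quality Assurance adds that "the responses will be checked for plausibility and consistency and inconsistent records will be documented and censored from the final analysis". It mentions implausibly short completion time as a sign of careless answering, gives no consistency rule, and does not say who makes the check.

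**The concern.** Participants know their arm and report the outcomes themselves, so analyst blinding is the only blinding that the article claims. It is worth most where the analysts must use judgement. The article leaves the level of sufficient exposure without a number, and that level defines the analysis it puts first.

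If controls do not play, game-use data are close to a label for the intervention arm. Analysts who hold them can work out the arm, and the same people hold the outcome. A report that repeated the Randomization statement would then claim more protection against biased choices than the analysis had.

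**Working it through.** The plan gives no figure on this point, so the main check sets the sections against each other. A short calculation then shows how much game-use data reveal.

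**Step 1. Which analyses need game-use data?**

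- *Exposure-based analysis:* needs them. Adherence also means different things by arm: playing enough in the intervention arm, not playing in the control arm. The rule cannot be applied without knowing which arm is which.
- *Adjusted regression:* needs the play count as written, beside the group term. It is fitted only if baseline differences are seen.
- *Intention-to-treat comparison of mean changes:* does not need them.
- *Follow-up plausibility check:* does not need them, but may expose them, because the game items belong to the same 4-week questionnaire.
- *Decision that baseline differences exist:* does not need them. Table 1 marks the user-experience items at follow-up only, and the logs arise during follow-up.

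**Step 2. How much does play reveal?** Inputs:

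- n = 190 per arm, from 380 participants allocated 1:1 (Sample Size Calculation).
- s = share of the intervention arm that plays at least once. Not given; assumed 30% to 100%.
- c = share of controls who play. Not given; assumed 0% to 20%. It may exceed zero because the game is publicly downloadable and downloading is separate from enrolment (Study Design and Hypotheses).

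*Without a group code*, call every player intervention and every non-player control. The share classified correctly is (s + 1 − c)/2:

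- s = 0.30, c = 0.20: (0.30 + 0.80)/2 = 0.55
- s = 0.70, c = 0.05: (0.70 + 0.95)/2 = 0.825
- s = 1.00, c = 0: (1.00 + 1.00)/2 = 1.00

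*With a masked A/B code*, compare the number of players under each code. The probability that the game arm shows more players is approximately Φ[(ns − nc)/√(ns(1 − s) + nc(1 − c))]. In the least favourable case, s = 0.30 and c = 0.20:

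- ns − nc = 57 − 38 = 19
- √(39.9 + 30.4) = 8.38
- 19/8.38 = 2.27, so the probability is 0.988

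Every other combination examined (s from 0.30 to 1.00, c from 0 to 0.20) gives 1.000 to three decimals. If only the 70% expected to complete follow-up are counted, n = 190 × 0.70 = 133 and the least favourable case is (39.9 − 26.6)/√(27.93 + 21.28) = 13.3/7.015 = 1.90, or about 0.97.

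**Step 3. Put together.** Play count alone labels individuals imperfectly. Play count with a group code identifies the code, and so the arm of every participant at once. The regression contains both by construction.

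**The case against.** A reader might infer that the blind is lost for each participant before any record is excluded or any model chosen. The documents do not support that.

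- They do not state the order of the steps, or that all variables sit in one file. Masked coding and staged release are details that an article may leave to a fuller document.
- Baseline differences can be judged on baseline data alone.
- The plausibility check is described under data quality with no actor named. It may be done by others, or without the game items.
- The regression with play count is conditional. The unadjusted comparison of mean changes comes first.
- Play count alone does not label everyone. Intervention participants who never play look like controls, and some controls may obtain the game. The questionnaire appendix is not shown, so it is unknown which game items controls see.
- Someone outside the analysis team could build the exposure-based set and pass on only a membership flag.
- The harm from open-ended choices comes mainly from the missing rules. Fixing those rules would remove most of it, whoever is blinded, and analyst blinding does nothing about self-report bias in an open trial.

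All of this limits the scope of the point. It does not remove the conflict: the article asserts blinding without limit and itself prescribes variables that defeat it. The play-count model needs arm and plays side by side, and no outside derivation of the exposure-based set is described.

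**Conclusion.** The blinding statement cannot hold for the play-count regression, nor for the exposure-based analysis if the analysis team builds that set itself, as the article reads. It is at risk, but not shown to fail, for the follow-up plausibility check. It is not threatened by the baseline-difference decision, and it can be kept for the intention-to-treat analyses.

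The size is one of identification, not of a shift in a planned figure. Under the assumed uptake and contamination, a masked code is resolved with probability of at least 0.988 at 190 per arm. The effect on the estimate or on the type I error cannot be derived from the documents, nor can the number of records that the plausibility check would remove. The point deserves action because the affected analysis is the one that the plan puts first, and its exposure threshold is open. The article describes the trial as not yet started, so the plan can still be changed before data exist.

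**What to change.** 1. Before any game-use data are released, fix in writing the plausibility and consistency rules, the adjustment model and the threshold for sufficient exposure. Setting the threshold at this stage is essential; otherwise it would be chosen by people who know both the arm and the results.
2. Give the analysts a file with a masked arm code and without login logs, play counts or user-experience items. Remove play count from the between-arm regression. Run and lock the intention-to-treat primary and secondary analyses on this file.
3. Then release the arm key and the game-use data for the as-treated and user-experience analyses, and label those as unblinded.
4. Reword the Randomization section so that analyst blinding covers the intention-to-treat analyses only.

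The cost is two data exports instead of one, a change to the covariate list, and a narrower blinding claim. No participants or assessments are added.
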